### Inclusion Criteria

Subjects will be enrolled after understanding and signing the informed consent form, ensuring their eligibility based on the provided inclusion or exclusion criteria.

Inclusion criteria must be fulfilled: (1) age 18 years or older, male or female; (2) availability of complete clinical information; and (3) agreement of the patient to join this study with signed consent and good compliance.

An additional specific inclusion criterion for subjects to be included in the malignant group must be fulfilled: confirmation of gastric adenocarcinoma through histopathology in accordance with the American Joint Committee on Cancer’s 8th Edition Cancer Staging Manual, with a pathological stage ranging from stage I to IV. This includes patients with esophageal gastric junction adenocarcinoma, regardless of histology types.

### Exclusion Criteria

Subjects will be considered ineligible if any of the following exclusion criteria are met: (1) they have previously been diagnosed with any kind of malignant tumor, (2) they have received total or partial gastrectomy, (3) they have received bone marrow or organ or stem cell transplantation, (4) they have received blood transfusion within the past 6 months, (5) they have previously received any form of local or systematic antitumor treatment, (6) they had ongoing fever or received anti-inflammation therapy within 14 days prior to blood draw for this study, (7) if female, they were pregnant or lactating, and (8) clinical information was incomplete or the subject was unqualified to participate in this study.

### Discontinuing Study Interventions and Patient Withdrawal

If the ongoing study is later considered to be infeasible, the principal investigator shall submit a termination application to the institutional review committee (IRC). The decision for the termination will be made by the IRC. Following the decision, the principal investigator shall provide a clinical trial termination report to the IRC.

Subjects may be withdrawn from this study for the following reasons: (1) subjects request to exit the trial and withdraw informed consent, (2) subjects refuse to have blood samples collected, even after providing informed consent, (3) sufficient blood sample collection is difficult for the subjects, and (4) subjects enrolled by mistake and are later assessed to be unsuitable for this study.

### Sample Collection

In total, 20 ml of peripheral blood will be collected from each subject and stored in a Cell-Free DNA Storage Tube (Cwbiotech). Each subject’s information, such as index, name, sample type, and collection time, will be marked clearly. Blood samples shall be delivered to the laboratory within 72 hours at 15 °C-35 °C to proceed with plasma extraction. In situations where timely delivery to the laboratory is not feasible, the blood samples shall be centrifuged at 4000 × g for 15 min at 4 °C and the upper layer containing plasma will be transferred to a new tube. Approximately 4 ml of plasma will be obtained and stored at −80 °C until use. Alternatively, for a period of no more than 1 month before transportation, the plasma can be stored at –20 °C.

### cfDNA Extraction

The plasma samples that were prepared in the previous step will be processed for cfDNA extraction by using the MagMAX Cell-Free DNA Isolation Kit (Thermo Fisher Scientific) per the manufacturer’s instructions. The quantity and quality of extracted cfDNA will be assessed with a Bioanalyzer 2100 (Agilent).

### WMS Library Construction

The entire amount of extracted plasma cfDNA (capped at 15 ng if exceeding what is needed) for each sample will be used to generate WMS libraries with the NEBNext Enzymatic Methyl-seq Kit (New England Biolabs) according to manufacturer instructions, with 1 modification: 100 ng of carrier RNA (TIANGEN) will be added before denaturation by sodium hydroxide. The generated libraries will be amplified with 9 polymerase chain reaction cycles, followed by quantification using the Qubit dsDNA HS Assay Kit (Thermo Fisher Scientific). After that, the constructed libraries will be subjected to sequencing on a NovaSeq 6000 system (Illumina) with a paired-end read length of 100 bp.

### Model Establishment

The estimation data set will be used to establish a machine learning model aimed at predicting cancer probability. Various features associated with plasma cfDNA fragments, such as their methylation status, will be subjected to data preprocessing, feature filtering, and model selection. This will lead to creation of respective classifier models. In a prior context, we defined these features as MFR, CAFF, FSI, and FEM.

#### MFR Feature

Genomic methylation status undergoes substantial alterations even in the early cancer development stage. The release of ctDNA by cancer cells can lead to changes in the methylation levels of cfDNA present in the plasma. To quantify these changes, the whole genome will be tiled into nonoverlapping 1 Mb windows. The methylation levels within each window will be quantified by the fraction of fragments featuring fully methylated CpGs, thereby resulting in the computation of MFR.

#### CAFF Feature

Cancer cells often exhibit chromosomal instability, with instances of partial or complete amplification or loss of chromosomal arms [29,30]. To account for this, a previously described plasma aneuploidy score will be calculated for each sample. This calculation will rely on the levels of copy number alterations in 5 specific chromosome arms, which exhibited the most significant copy number alterations when compared to baseline samples [20].

#### FSI Feature

The size frequency of ctDNA fragments released from cancer cells differs from that of cfDNA [31]. By tiling the whole genome into nonoverlapping 1 Mb windows, the read ratio between short fragments (100-166 bp) to long fragments (169-240 bp) will be computed, resulting in the determination of the FSI. Subsequently, the FSI of each sample will be contrasted with the healthy population baseline, and the cancer risk for each subject will be estimated.

#### FEM Feature

The preferred FEMs of ctDNA differ from those of cfDNA due to DNA nuclease downregulation in the cfDNA fragmentation process [31]. The frequency of a total of 256 4-nucleotide (ie, 4-mer) fragment 5’ end motifs will be analyzed, with the following modifications: (1) only fragments shorter than 171 bp will be selected for analysis, and (2) only reads mapped to the Crick strand will be used for calculation.

An ensemble classifier named THEMIS has been developed based on a generalized linear model incorporating elastic-net penalization. THEMIS is established by integration of the 4 abovementioned features, which includes the predicted cancer probability scores by MFR, FSI, and FEM along with the plasma aneuploidy scores of CAFF. R packages such as *CARET* under 20-fold cross validation will be used.

### Sample Size Estimate and Statistical Analysis

The sample size was estimated using the strategy mentioned by Negida et al [32]. Based on the abovementioned pilot study, the ensemble THEMIS model reached a sensitivity of 0.94 with 0.95 specificity (Figure 1). We expect that the new model integrating similar features as THEMIS will attain a sensitivity of at least 0.9. If we consider the 95% CI width of 0.08 (2-sided test α=.05), then at least 54 cancer cases will be required. If we also expect a certain amount of dropout, such as 10%, a minimum of 60 cases will be needed. The same number of patients will be enrolled in the nonmalignant control group for this case-control study. The plan is to allocate both groups of subjects by the same 2:1 ratio into training and testing data sets. Ensuring at least 60 cases and 60 controls within the testing data set, a total of 360 subjects (180 cancer cases and 180 controls) will be enrolled. This ensures that each group is composed of no fewer than 180 subjects. The malignant group and the control group will be matched by age and sex to minimize possible confounding factors (Figure 2).

The area under the curve, constructed with a receiver operator characteristic analysis calculated by the *pROC* package, will be used to evaluate individual classifier models as well as the ensemble model’s performance in distinguishing between cancer and noncancer conditions. Clinical diagnosis results, including but not limited to gastroscopy or pathological determinations, are considered the “gold standard.” The cancer risk threshold (cutoff value) will be determined based on the training data set. After that, the prediction performance of the established model will be evaluated in the testing data set in several aspects, including sensitivity, specificity, positive prediction value, and negative prediction value. These variables, as well as 95% CI, will be calculated using the *epiR* package. The Cohen κ score will be calculated with the *vcd* R package to demonstrate the concordance of the predicted results versus the pathological diagnostic results. A single-blind analysis will be applied, which means that the bioinformatics analysts will be blinded to whether the subjects have GC or not. The results are considered significant if the *P* value is <.05. All statistical analyses will be performed in R (version 3.6.3; R Core Team).

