We have also previously developed a multidimensional ensemble model named Thorough Epigenetic Marker Integration Solution (THEMIS). This model integrates various cfDNA features, including methylated fragment ratio (MFR), chromosomal aneuploidy of featured fragments (CAFF), fragment size index (FSI), and fragment end motif (FEM), enabling highly sensitive early detection across a pan-cancer cohort [27]. In a subgroup comprising 114 patients with GC and 497 healthy controls, the THEMIS model showed an estimated area under the curve of 0.983 for the training data set (Figure 1A) and 0.986 for the test data set (Figure 1B). However, the fact that the model was trained on a pan-cancer cohort and the control group did not contain individuals with benign gastric diseases limits its predictive reliability for GC.

This study aimed to develop a highly sensitive GC-specific THEMIS model for the early detection of GC. This study’s design is illustrated in Figure 2. Patients with GC will be enrolled in the malignant group, while the control group will comprise not only healthy individuals but also participants with benign gastric diseases, such as gastritis, gastric ulcers, and gastric polyps. Consequently, a novel model will be developed to differentiate malignant cancer from nonmalignant gastric status. A nonbisulfite enzymatic whole methylome sequencing (WMS) assay [28] will be applied to ensure the preservation of methylation signals from the cfDNA alongside the molecular fragmentation profile. The sequencing data generated from cfDNA will then be analyzed across the abovementioned multiple dimensions, encompassing methylation patterns, chromosomal copy number alterations, and fragmentation profiles. In addition, GC-related biomarkers, such as PG, G-17, and *H pylori*, will be evaluated either independently or in combination with cfDNA features during model training to enhance the detection sensitivity. The overall clinical performance of the model, as well as its performance in each clinical stage, will be evaluated.

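### The 0.08 given as the 95% CI width behind the 54 cases is a half-width; the interval for sensitivity will be about 0.16 wide

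*Protocol article*

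**What the plan says.** All of the reasoning is in the protocol article under Sample Size Estimate and Statistical Analysis. It takes its planning value from the pilot model (sensitivity 0.94 at specificity 0.95), lowered to 0.9: "We expect that the new model integrating similar features as THEMIS will attain a sensitivity of at least 0.9". It then sets the precision target and the number of cases: "If we consider the 95% CI width of 0.08 (2-sided test α=.05), then at least 54 cancer cases will be required". Dropout is added: "If we also expect a certain amount of dropout, such as 10%, a minimum of 60 cases will be needed". Controls are set equal in number: "The same number of patients will be enrolled in the nonmalignant control group for this case-control study". Both groups are split in the same way: "The plan is to allocate both groups of subjects by the same 2:1 ratio into training and testing data sets". The total follows: "Ensuring at least 60 cases and 60 controls within the testing data set, a total of 360 subjects", that is, 180 cases and 180 controls.

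The section nowhere calls 0.08 a half-width or a margin of error, and does not write it with a plus-or-minus sign. It also says that sensitivity and specificity will be estimated in the testing data set with 95% confidence intervals.

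**The concern.** The width of a confidence interval is the distance from its lower to its upper limit. On that meaning, a width of 0.08 around 0.90 tells the reader to expect limits of roughly 0.86 and 0.94. Fifty-four cases are far too few for that, so either the width or the number of cases is misstated.

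Validating overall sensitivity and specificity is the primary objective (Study Objectives), and this sentence is the only quantitative justification for the size of the test set. Anyone judging from the article whether the study is large enough would credit its sensitivity estimate with about twice the precision that it can deliver.

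**Working it through.** **Inputs**, all from Sample Size Estimate and Statistical Analysis: sensitivity p = 0.90; 95% confidence, two-sided α = 0.05, so z = 1.96; stated width 0.08; stated requirement 54 cases; dropout 10%; 2:1 split into training and testing.

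**Formula.** For one proportion under the normal approximation (Wald), n = z² p(1 − p) / d², where d is the half-width.

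**Step 1: reproduce the plan's figure.** With d = 0.08, n = 3.8416 × 0.09 / 0.0064 = 54.02, the stated 54 (strict rounding up would give 55, which is immaterial). Then 54 / 0.9 = 60 cases after dropout, 60 × 3 = 180 per group, and 2 × 180 = 360. The whole chain is reproduced with 0.08 as the half-width.

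**Step 2: take the sentence as printed.** A full width of 0.08 means d = 0.04, and n = 3.8416 × 0.09 / 0.0016 = 216.1, so 217 evaluable test-set cases. Adding 10% dropout gives 217 / 0.9 = 241.1, so 242; under the 2:1 split that is 3 × 242 = 726 cases, against 180 planned.

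**Step 3: look for another reading that gives 54 at full width 0.08.**
- p = 0.94 (pilot sensitivity): 136 cases.
- p = 0.95: 115 cases.
- One-sided z with p = 0.90: 152.2 cases.
- The sensitivity would have to be about 0.977 for 54 cases to give a full width of 0.08.
- Even all 180 cases, training and testing together, would give a width of 0.088 at p = 0.90.

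None of these matches the plan's inputs.

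**Step 4: the precision that the planned test set gives at sensitivity 0.90.**

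| Evaluable cases | Wald half-width | Wald limits | Wald width | Wilson width | Exact width |
|---|---|---|---|---|---|
| 54 | 0.080 | 0.820 to 0.980 | 0.160 | 0.163 | 0.177 |
| 60 | 0.076 | 0.824 to 0.976 | 0.152 | 0.155 | 0.167 |

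Against the printed 0.08, the Wald width is 0.160 / 0.08 = 2.0 times as large with 54 cases and 0.152 / 0.08 = 1.9 times with 60. As a concrete result, 54 of 60 cases detected gives an exact (Clopper-Pearson) 95% interval of 0.795 to 0.962.

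**The case against.** The strongest reply is that this is a slip of terminology. The numbers from 54 to 360 are consistent if the authors planned for ±0.08, and that is the likeliest explanation. The sample-size source that the article cites is not at hand and may use the word width for the margin of error. The article also commits to reporting 95% confidence intervals, so the eventual reader of the results will see the true precision.

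Most of this stands, and it limits the point to the stated precision. It does not remove it. Whatever the source's vocabulary, a confidence interval 0.08 wide and 54 cases at sensitivity 0.9 cannot both be true as printed. Nor does condensation into an article explain it, because this is a figure given wrongly and not a detail left out.

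A reader might be tempted to infer more, and the article does not support it:

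- *That specificity is also planned to 0.08.* The figure is attached only to sensitivity and cancer cases; controls are simply set equal in number. At the pilot specificity of 0.95 the Wald half-width would be about 0.058 with 54 controls and 0.055 with 60.
- *That the test set cannot support a sensitivity of at least 0.9.* That value is a planning expectation, with no null value or lower-bound criterion attached. Nor is it out of reach: 59 of 60 detected would give an exact lower limit of 0.911.
- *That the pilot invalidates the planning value.* The Introduction says that pan-cancer training and the lack of controls with benign gastric disease "limits its predictive reliability for GC". It says this of the earlier model and gives it as the reason for the present study; the plan already lowers 0.94 to 0.9.

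**Conclusion.** The sentence is wrong as written. At sensitivity 0.90, 54 cases give a 95% interval of about ±0.08, with total width about 0.16. The plan therefore overstates the precision of sensitivity by a factor of 2.0 with 54 evaluable cases and 1.9 with all 60. In numbers of cases, the printed width would need about four times as many (217 against 54).

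That fourfold ratio should not be read as proof that the study is undersized. It measures the plan against the printed word, whereas the plan's own arithmetic points to ±0.08 as the intended target. The article does not say which was meant. The conclusion rests on the normal approximation, which reproduces the plan's 54, and on a sensitivity of 0.90; the Wilson and exact intervals are somewhat wider still.

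**What to change.** Keep the total at 360 and correct the sentence, for example: *54 evaluable test-set cases give a 95% CI of about plus or minus 0.08 (total width about 0.16) at sensitivity 0.90.* Add the exact interval for one plausible result as an illustration (54/60: 0.795 to 0.962). Showing the precision at a sensitivity of 0.80 to 0.85 as well is optional: the Wald half-width with 54 cases is 0.107 at 0.80 and 0.095 at 0.85.

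The cost is one sentence and no extra patients; the downside is that the stated precision becomes less favourable. Only if a total width of 0.08 was truly intended would the test set have to grow, to about 217 evaluable cases.

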**Methods:**

This is an observational case-control study. Blood samples will be prospectively collected before gastroscopy from 180 patients with GC and 180 nonmalignant control subjects (healthy or with benign gastric diseases). Cases and controls will be randomly divided into a training and a testing data set at a ratio of 2:1. Plasma cfDNA will be isolated and extracted, followed by bisulfite-free low-depth whole methylome sequencing. A multidimensional model named Thorough Epigenetic Marker Integration Solution (THEMIS) will be constructed in the training data set. The model includes features such as the methylated fragment ratio, chromosomal aneuploidy of featured fragments, fragment size index, and fragment end motif. The performance of the model in distinguishing between patients with cancer and noncancer controls will then be evaluated in the testing data set. Furthermore, GC-related biomarkers, such as pepsinogen, gastrin-17, and *Helicobacter pylori*, will be measured for each patient, and their predictive accuracy will be assessed both independently and in combination with the THEMIS model

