## Discussion

The primary aim of this study was to evaluate the effectiveness of using combined cfDNA features, determined through WMS analysis, for early cancer detection. If our model is incorporated into current clinical practices, an individual with a positive result would subsequently undergo either a gastroscopy, a biopsy, or both to ascertain the presence of GC. Conversely, a negative result would indicate a low likelihood of GC and prompt recommendations for a deferred gastroscopy, along with the possibility of an annual repeated test.

The major strength of this study is that this is the first registered observational study, to our knowledge, designed to evaluate the integrated analysis of methylation patterns, fragmentation profiles, and chromosomal copy number changes in cfDNA for early GC detection. Additionally, cfDNA studies designed for the Chinese GC population are limited. Our study will reveal whether multidimensional analysis of cfDNA is an effective strategy for differentiating patients with GC from nonmalignant individuals in the Chinese population.

This study has several potential limitations. Foremost among these is the fact that it is a case-controlled study with a relatively modest cohort size. We acknowledge that case-control studies, especially those performed at a single site, are susceptible to selection bias. Individuals enrolled from a single hospital may not be fully representative of the diversity of a general screening population. Given these limitations, a comprehensive and sizable prospective validation within a screening population will be pursued prior to considering clinical implementation. Another limitation would be that it is impossible to include all the possible benign gastric disease types in the control group; therefore, the constructed model might have limited ability to differentiate GC from other types of benign diseases beyond this study. In addition, although the individuals will be prospectively enrolled in this study, the analysis will be carried out retrospectively. However, it is notable that the bioinformatics analysts will remain blinded to the true pathological outcomes during the validation of the model in the testing cohort, thereby mitigating the potential analysis bias.

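### PPV, NPV and Cohen kappa taken from a 1:1 case-control testing set reflect a 50% case fraction fixed by design and do not estimate values in a gastroscopy or screening population

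*Protocol article*

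**What the plan says.** The Methods part of the Abstract in the protocol article plans to enrol "180 patients with GC and 180 nonmalignant control subjects". Sample Size Estimate and Statistical Analysis gives the same totals ("a total of 360 subjects (180 cancer cases and 180 controls) will be enrolled") and makes the equal group sizes a design choice: "The same number of patients will be enrolled in the nonmalignant control group for this case-control study". It then plans to "allocate both groups of subjects by the same 2:1 ratio into training and testing data sets", with the aim stated as "Ensuring at least 60 cases and 60 controls within the testing data set".

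The same section says the model will be "evaluated in the testing data set in several aspects, including sensitivity, specificity, positive prediction value, and negative prediction value". It assigns the estimates and their 95% confidence intervals to the epiR package. Cohen kappa is added "to demonstrate the concordance of the predicted results versus the pathological diagnostic results". It names no target prevalence, no reweighting and no limit on how these three measures may be interpreted.

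Study Objectives and the Discussion describe the intended use. People who test positive go on to gastroscopy, while "a negative result would indicate a low likelihood of GC and prompt recommendations for a deferred gastroscopy".

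The primary objective is sensitivity and specificity, overall and by stage. The secondary objective is the same two measures with serological markers added.

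**The concern.** Participants are counted into the study by disease status until each group reaches its quota. The proportion with cancer in the testing set is therefore chosen by the sponsor and says nothing about any population. Sensitivity and specificity are conditional on disease status and remain estimable under such sampling. PPV, NPV and kappa depend on the mix of cases and controls, so their values in the testing set describe only that mix.

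This matters because the intended use turns on what a positive or a negative result means for the person tested, and predictive values are the measures that express this. A reader who wants to know how many positives would prove to have cancer will look at the reported PPV. That figure, with its confidence interval, would apply to a setting in which every second person tested has gastric cancer.

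**Working it through.** **Inputs**
- Case fraction in the testing set: 60 of 120, from the equal groups and the common 2:1 split (Sample Size Estimate and Statistical Analysis).
- Sensitivity (Se) 0.90: the value the same section expects the new model to reach at least.
- Specificity (Sp) 0.95: the pilot value in the same section. That the new model keeps it is an assumption.
- Prevalence p in the intended-use population: not given in the document. It is varied below as an assumption.

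**Step 1: the plan's own figure.** For one proportion, n = 1.96² × 0.90 × 0.10 / 0.08² = 54.02. This matches the stated 54 when 0.08 is read as the half-width of the interval. Allowing for 10% dropout, 54/0.90 = 60. With one third of each group in the testing set, 60 × 3 = 180 per group. The chain reproduces and confirms a 60:60 testing set. Equal dropout in the two groups would leave the fraction at 50%.

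**Step 2: the table the plan would produce.** Of 60 cases, 0.90 × 60 = 54 test positive and 6 negative. Of 60 controls, 0.95 × 60 = 57 test negative and 3 positive.
- PPV = 54/57 = 94.7% (exact 95% CI 85.4% to 98.9%).
- NPV = 57/63 = 90.5% (exact 95% CI 80.4% to 96.4%).
- Kappa: observed agreement is (54 + 57)/120 = 0.925 and chance agreement is 0.5 × 0.475 + 0.5 × 0.525 = 0.50, so kappa = 0.425/0.50 = 0.85.

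**Step 3: the same test at other prevalences.**
- PPV = Se·p / [Se·p + (1 − Sp)(1 − p)]
- NPV = Sp(1 − p) / [Sp(1 − p) + (1 − Se)p]
- Kappa = (po − pe)/(1 − pe), where po = Se·p + Sp(1 − p), q = Se·p + (1 − Sp)(1 − p), and pe = p·q + (1 − p)(1 − q)

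Worked at p = 0.01:
- PPV = 0.0090/(0.0090 + 0.0495) = 0.154
- NPV = 0.9405/(0.9405 + 0.0010) = 0.999
- po = 0.9495, q = 0.0585, pe = 0.9327, so kappa = 0.25

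| Prevalence | PPV | NPV | Kappa | PPV at 50% ÷ this PPV |
|---|---|---|---|---|
| 50% (by design) | 94.7% | 90.5% | 0.85 | 1 |
| 20% (assumed) | 81.8% | 97.4% | 0.82 | 1.2 |
| 10% (assumed) | 66.7% | 98.8% | 0.74 | 1.4 |
| 5% (assumed) | 48.6% | 99.4% | 0.61 | 1.9 |
| 1% (assumed) | 15.4% | 99.9% | 0.25 | 6.2 |
| 0.1% (assumed) | 1.8% | 99.99% | 0.03 | over 50 |

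Even at an assumed 20%, PPV (81.8%) lies below and NPV (97.4%) lies above the intervals in Step 2.

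**Step 4: sensitivity of the result to the inputs.** With the pilot sensitivity of 0.94 in place of 0.90, PPV is 94.9% at 50%, 67.6% at 10%, 16.0% at 1% and 1.8% at 0.1%. The pattern is the same.

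**The case against.** The strongest reply is that nothing the study sets out to show depends on these measures. Both objectives are framed as sensitivity and specificity, and the sample size rests on sensitivity. PPV, NPV and kappa appear as further descriptors, with no hypothesis or success criterion attached. This stands. A reader might infer that the main results are compromised, but sensitivity, specificity and AUC do not depend on the case fraction.

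Second, the error in NPV is conservative. A reader might infer that the Discussion's statement about negative results is inflated. On these inputs the opposite holds: NPV rises from 90.5% to 99.4% at an assumed 5% and higher below that. Only PPV errs in the favourable direction, and the stated consequence of a positive result is confirmation by gastroscopy or biopsy.

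Third, a reader might infer that PPV is inflated several-fold as a matter of fact. The document gives no prevalence, enrols people who attend for gastroscopy, and speaks of identifying high-risk patients. The factor is 1.4 at 10% and 1.9 at 5%, and reaches about 6 only near 1%. The direction is certain below 50%, but the size is conditional. Nor would the intervals be tight: they are 13 to 16 percentage points wide at 60:60. Their fault is what they are centred on.

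Fourth, the Discussion names the case-control design as the foremost limitation, doubts that one hospital represents a screening population, and promises prospective validation before clinical use. This tempers any clinical claim. It concerns selection and representativeness, however, and does not say that PPV, NPV and kappa are set by the 1:1 ratio, so it does not correct the planned analysis.

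Finally, the article is condensed, and a fuller plan might adjust for prevalence. That the calculation is a raw one is an inference. It is the natural reading, because the data set, the measures and the software are all named and no prevalence input is mentioned.

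**Conclusion.** The point holds as one about additional performance measures, and it should be fixed. As written, PPV, NPV and kappa would come from a testing set that is 50% cancer by design, and they would not estimate the values in a gastroscopy or screening population. At sensitivity 0.90 and specificity 0.95, PPV would be reported as 94.7%, against 66.7% to 1.8% over assumed prevalences of 10% to 0.1%. NPV would be 90.5%, against 98.8% to 99.99%, and kappa 0.85, against 0.74 to 0.03.

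These sizes assume that the new model keeps the pilot specificity, that test-set sensitivity and specificity carry over to the target population, and that prevalence lies in the range shown. The document does not support a stronger conclusion that the primary or secondary results, the sample size or the study design are affected.

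**What to change.** Replace the raw test-set PPV and NPV with values computed by Bayes' theorem from test-set sensitivity and specificity, tabulated over a range of target prevalences stated in advance. The range could include the hospital's own gastric cancer yield at gastroscopy, if it can be obtained, and lower values for screening, such as 0.1% to 5%. Propagate the intervals from the uncertainty in sensitivity and specificity. One way is through the likelihood ratios: post-test odds equal pre-test odds times the ratio. Here the positive ratio is 0.90/0.05 = 18.

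Drop kappa, or keep it with a label. Any kappa, or any raw PPV or NPV that is retained, should be marked as specific to the 1:1 sample and as not supporting claims about clinical use. One sentence in the limitations should say that these measures depend on the sampled case fraction.

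The cost is a few lines of analysis text and code. No new data and no design change are needed. The reported PPV will look less favourable, and NPV more favourable, than in the raw table.
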